## Abstract

**Background:**

Patients with Chronic Tension Type Headache (CTTH) report functional and emotional impairments (loss of workdays, sleep disturbances, emotional well-being) and are at risk for overuse of medication. Manual therapy may improve symptoms through mobilisation of the spine, correction of posture, and training of cervical muscles.

We present the design of a randomised clinical trial (RCT) evaluating the effectiveness of manual therapy (MT) compared to usual care by the general practitioner (GP) in patients with CTTH.

**Methods and design:**

Patients are eligible for participation if they present in general practice with CTTH according to the classification of the International Headache Society (IHS).

Participants are randomised to either usual GP care according to the national Dutch general practice guidelines for headache, or manual therapy, consisting of mobilisations (high- and low velocity techniques), exercise therapy for the cervical and thoracic spine and postural correction. The primary outcome measures are the number of headache days and use of medication. Secondary outcome measures are severity of headache, functional status, sickness absence, use of other healthcare resources, active cervical range of motion, algometry, endurance of the neckflexor muscles and head posture. Follow-up assessments are conducted after 8 and 26 weeks.

**Discussion:**

This is a pragmatic trial in which interventions are offered as they are carried out in everyday practice. This increases generalisability of results, but blinding of patients, GPs and therapists is not possible.

The results of this trial will contribute to clinical decision making of the GP regarding referral to manual therapy in patients with chronic tension headache.

## Background

The 1-year prevalence of Chronic Tension-Type Headache (CTTH) is about 2–5% in the general population. In half of the CTTH cases, headache-related impairment in work performance is reported. [1,2] In addition to considerable impact on daily functioning and work participation, CTTH is a risk factor for overuse of analgesic medication [3]. Only about 20% of the CTTH patients seek medical care for their headache. This low consultation rate may be explained by insufficient information on the effectiveness of treatments or by previous negative health care experiences.[1,4]

In primary care treatment for patients with CTTH is often provided by the general practitioner (GP). The Dutch national general practice guideline for the management of headache describes diagnostic and therapeutic algorithms, consisting mainly of reassurance, lifestyle advice and medication.[5] The effectiveness of this guideline for patients with CTTH has not been investigated.

The pathogenesis of CTTH remains unclear. Pathophysiological theories considering central and peripheral pain mechanisms are described and have been discussed in the literature. [6] In recent research a correlation between CTTH and impairment of the cranio-cervical musculoskeletal function (forward head position, trigger points trapezius muscle, neck mobility) has been demonstrated [7-10] In combination with results obtained in previous studies the present data support the hypothesis that improvement of the cranio-cervical musculoskeletal function by a manual therapy intervention (postural correction, mobilisation cervical spine, and training of cervical muscles) may be an important factor to modify central or peripheral pain mechanism in CTTH. [11-15]

Three randomized clinical trials have investigated the effectiveness of manual therapy in patients with CTTH and reported benificial effects.[16-18]. However, because of variation in inclusion criteria, treatment techniques (high-, low velocity mobilization, exercises, traction), and small sample sizes there is insufficient evidence to support the use of manual therapy in the treatment of CTTH. Well-designed clinical trials are recommended to provide more substantial evidence for the effectiveness of manual therapy. [19,20]

## Design

We aim to conduct a pragmatic, multicentre, randomised clinical trial, assessing the effectiveness of manual therapy (MT) compared to usual GP care in patients with CTTH. We have used the guidelines of the International Headache Society (IHS) for the design of randomised clinical trials for headache to develop the randomisation procedure, outcome measurements and statistical analysis.[21] The procedures and design of this study are approved by the Medical Ethics Committee of the VU University Medical Center in Amsterdam, The Netherlands. (Trial registration number TR 1074)

### Study population

Participating primary healthcare centers and GPs in an urban area in the Netherlands, will invite patients with headache to participate in the trial.

Patients between 18 and 65 years of age are invited if they have CTTH according to the classification of headaches of the IHS [22]: headache occuring on at least 15 days on average per month for a period of more than 3 months (≥ 180 days a year) and lasts for hours or may be continuous. The headache has at least one of the following characteristics: 1. bilateral location, 2. pressing/tightening (non pulsating) quality, 3. mild or moderate intensity, not aggravated by normal physical activities such as walking or climbing stairs; and both of the following: 1. no more than one of photofobia, phonophobia or mild nausea, and 2. neither moderate or severe nausea nor vomiting. Participants should be able to read and write Dutch.

Exclusion criteria include reumatoid arthritis, suspected malignancy, pregnancy, intake of either triptans, ergotamines or opioids on ≥ 10 days/month or simple analgesics on ≥ 15 days/month on a regular basis for ≥ 3 months, and having received manual therapy treatment in the 2 months before enrolment into the study.

After the GP has seen a patient with CTTH the patient receives an information letter about the trial. If the patient is willing to participate after reading the information he or she can contact the research centre. A researcher will screen interested patients by telephone and make an appointment to check inclusion and exclusion criteria, and complete the informed consent procedure. After written informed consent has been obtained, the baseline measurement is carried out. The design of the trial is explained in Figure 1.

**Figure 1 F1:**
[figure not shown]
**Flow chart, representing the design of the trial on Chronic Tension Type Headache (CTTH)**.

### Baseline assessment

Table 1 shows the outcome measures and the time points at which they are assessed. At baseline we will collect additional information on demographic variables including age, gender, date of birth, education and occupation. The patient will also be asked to score expectations regarding the effectiveness of treatment on a 7-point rating scale (no result at all to very good result). In a standardised history taking procedure including the two-week headache-diary, the diagnosis of CTTH according to the diagnostic criteria of the IHS guideline will be confirmed.[22]

**Table 1 T1:** Summary of data collection.

	**Baseline**	**After 8 weeks**	**After 26 weeks**	**Measurement**
Sociodemographics	X			Single items

Treatment expectations	X			7-point rating scale

**Primary outcome measures**				

Headache frequency	X	X	X	Headache diary

Medication use	X	X	X	Headache diary

**Secondary outcome measures**				

Headache pain intensity	X	X	X	10 points scale

Headache Impact on daily life	X	X	X	HIT-6 HDI

Active range of movement Cervical spine	X	X	X	CROM

Algometry M. Trapezius and suboccipital muscles	X	X	X	Algometer

Craniocervical angle	X	X	X	Digital photo

Endurance neck flexor muscles	X	X	X	Neck flexor endurance test

Use of health care resources			X	Checklist

### Randomisation

Randomisation will take place after baseline measurement by the research assistant. Before the start of the trial a random sequence has been composed using computer-generated random numbers. Allocation is carried out by the research assistant who has not been informed about the random sequence, by giving the patient a numbered and sealed envelope.

The patient will open the envelope in the presence of another independent administrative assistant, who will subsequently make an appointment for the first treatment session either by the patient's own GP, or by one of the participating manual therapists.

### Blinding

GPs and manual therapists cannot be blinded for treatment allocation, but will not be informed about the results of outcome measurements. The research assistant is kept blind for the patient's treatment allocation.

Data collection and administration will by carried out by an independent data assistent. The researcher is involved in the statistical analysis, but the analysis and interpretation of the findings will be audited and verified by an independent statistician.

### GP intervention

Patients will be treated by the GP according to the national clinical guideline for the management of headache [5]. According to this guideline the GP will provide information, reassurance and advice and will discuss the benefits of lifestyle changes. If necessary, GPs may prescribe analgesics or non- steroid anti-inflammatory drugs (NSAID) or change current pain medication.

### Manual Therapy intervention

MT treatment will include a combination of mobilisation of the cervical and thoracic spine, exercises and postural correction based on the management of cervicogenic headache. [23] Spinal mobilisations will consist of low and/or high-velocity cervical and thoracic joint mobilization and manipulation techniques. Therapeutic exercises consist of low-load craniocervical muscle endurance exercises and correction of sitting and standing posture. The participating MT's are registrated MT's and member of the national association of manual therapists. They have an average experience of 10 years as manual therapist and have completed the McKenzie B-course on the cervical spine. In two meetings the MTs have been trained in the treatment protocol, they have received a manual and patient-booklets with home exercises.

Depending on the patient's condition the MT can decide what type of techniques and exercises will be selected from the protocol. The MT will make a report of the treatment modalities used in each session.

The MT intervention is restricted to a maximum of 9 sessions (each 30 minutes) in 8 weeks after randomisation.

### Primary outcome measures

The follow-up measurements will take place by a blinded research assistant immediately after the 8 weeks treatment period and after 26 weeks (long term follow-up). Two weeks before each measurement the patients receive and complete a two-week headache diary. The primary outcome measures are 1) the frequency of days with headache, and 2) use of pain medication (no. of doses NSAIDs or simple analgesics). Registration over a two week period is considered to be sufficient.[24]

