### Sample size

In a pilot study the 2 weeks headache diary showed an average of 11 days with headache in both treatment groups at baseline. After 8 weeks the frequency of days with headache in the GP group was reduced to 7 days, in the MT group to 3 days. In the full trial we aim to detect a difference in reduction of at least 3 days (SD 5) between both groups. To detect this difference with a one-sided significance level of 0.05, and power of 0.80 we have to include at least 35 patients in each treatment group. The participants in the pilot study reported taking on average 2 doses of NSAID or analgesics per 2 weeks. With a sample size of 35 patients per group we can detect a difference of at least 0.5 (SD 0.8) doses per 2 weeks between the groups. With a calculated loss of participants in the full trial of 15%, this trial attempts to enroll forty-two patients with CTTH in each treatment groups (GP, MT).

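### Two primary outcomes are each sized at the full one-sided 0.05, with no primary time point named and no statement of whether one or both must succeed

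*Protocol article*

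**What the plan says.** The section on primary outcome measures reads: "The primary outcome measures are 1) the frequency of days with headache, and 2) use of pain medication". The abstract and Table 1 agree. Both outcomes come from a two-week diary, and follow-up takes place "immediately after the 8 weeks treatment period and after 26 weeks (long term follow-up".

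The sample size section starts from pilot data at 8 weeks: "After 8 weeks the frequency of days with headache in the GP group was reduced to 7 days", against 3 days in the manual therapy group. It continues "we aim to detect a difference in reduction of at least 3 days (SD 5) between both groups", and concludes that "with a one-sided significance level of 0.05, and power of 0.80 we have to include at least 35 patients in each treatment group". For medication, the same 35 per group is said to suffice: "we can detect a difference of at least 0.5 (SD 0.8) doses per 2 weeks between the groups". After allowing for 15% loss, the target is 42 per group.

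The statistical analysis section plans between-group differences in change, with 95% confidence intervals and a t-test or non-parametric test, for all primary and secondary outcomes. The article gives no order of testing, no division of alpha and no rule for combining the two primary outcomes.

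**The concern.** With two primary outcomes, the trial's error rate and power depend on how the two results are combined. If success on either is enough, the chance of at least one false positive exceeds the nominal level. If success on both is required, the error rate is safe but the chance of success falls below the power of each test. The plan does not say which applies, and a second follow-up visit adds a further choice.

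Silence on multiplicity in a journal article can often be left to the analysis plan. Here the article has already committed the alpha: its sample size is derived with the full one-sided 0.05 for headache days and is then reused without change for doses. A later analysis plan could not divide alpha, or require both outcomes, and still have 80% power from 35 per group.

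The results are meant to inform referral decisions by general practitioners. Without a rule, an effect on medication use alone, or at 26 weeks alone, could be presented as the primary finding.

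**Working it through.** **Inputs.** From the sample size section: one-sided alpha 0.05; power 0.80; 35 per group; 3 days (SD 5); 0.5 doses (SD 0.8); 15% loss. From the abstract, Table 1 and the section on primary outcome measures: two outcomes and two follow-up times. Correlations between outcomes and between visits are not given. They are assumed below and shown as ranges.

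**1. The plan's own figures.** n per group = 2(z_alpha + z_beta)² SD² / difference².
- Headache days: 2 × (1.645 + 0.842)² × 25/9 = 34.3, so 35. With loss, 35/0.85 = 41.2, so 42. Both stated figures reproduce.
- Doses: 2 × (1.645 + 0.842)² × 0.64/0.25 = 31.7, so 32. Thirty-five is enough.
- Power at 35 per group (t-test, 68 df, noncentrality d√(35/2)) is 0.800 for days (d = 3/5 = 0.6) and 0.827 for doses (d = 0.5/0.8 = 0.625) at one-sided 0.05. At two-sided 0.05 it is 0.697 and 0.732.

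Each outcome therefore has its stated power, provided each keeps the full one-sided 0.05.

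**2. Error rate if one significant result is enough.** This is the chance of at least one false claim for manual therapy when neither outcome has a true effect. With k independent tests it is 1 − (1 − a)^k, where a is the error of each test in that direction. Correlated cases use a multivariate normal distribution.

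| Tests that count | Assumed correlation | a = 0.05 (one-sided) | a = 0.025 (95% CI) |
|---|---|---|---|
| One test | – | 5% | 2.5% |
| Two outcomes, 8 weeks | 0 | 1 − 0.95² = 9.75% | 1 − 0.975² = 4.9% |
| | 0.3 | 9.3% | 4.8% |
| | 0.5 | 8.8% | 4.5% |
| | 0.9 | 6.8% | 3.5% |
| Two outcomes, 8 and 26 weeks | outcomes 0.3-0.5, times 0.5-0.7 | 13.8-15.9% | 7.4-8.5% |
| | all independent (ceiling) | 1 − 0.95⁴ = 18.5% | 1 − 0.975⁴ = 9.6% |

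**3. Power if both must succeed at one time point, 35 per group.** Bivariate normal with the marginal powers from step 1.
- One-sided 0.05: 0.800 × 0.827 = 66% at correlation 0, 69% at 0.3 and 71% at 0.5.
- Two-sided 0.05: 0.697 × 0.732 = 51% at correlation 0, 55% at 0.3 and 57% at 0.5.

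**4. Size if alpha were divided instead.** One-sided 0.025 per outcome needs 2 × (1.960 + 0.842)² × 25/9 = 43.6, so 44 per group for headache days. With loss, 44/0.85 = 51.8, so 52.

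**The case against.** The strongest reply is that the article nowhere says that any one of four tests proves effectiveness. That is right. A reader might infer a plan with a false-positive rate of 19%, but the text does not support it. The figure needs an any-of-four rule that is not written. It also needs independence between visits that use the same patients and subtract the same baseline.

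The time point is also partly settled by context. Manual therapy is confined to 8 weeks, the pilot effect is an 8-week effect, and 26 weeks is labelled long-term follow-up. This makes 8 weeks the natural main time point and two tests the fairer count. It remains an inference: the discussion also says that the programme aims at a lasting effect, which would suit a 26-week claim.

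A reader might further infer that the stated alpha and power contradict each other. Outcome by outcome they do not: both powers reproduce, and the article claims neither family-wise error control nor joint power.

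Finally, the one-sided 0.05 appears only in the sample size section, while the analysis section plans 95% intervals. Judged by those intervals, the inflated rates are roughly half as large, as the table shows.

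These points lower the figures and narrow the claim. They do not supply the missing rule.

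**Conclusion.** The point stands in limited form. The sample size is calculated correctly, but it gives each of two primary outcomes the full one-sided 0.05 without saying whether one or both must succeed, or at which visit.

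- **Either outcome, 8 weeks:** about 7-10% at one-sided 0.05, or about 4-5% judged by the 95% interval against 2.5% for one test. This assumes outcome correlation between 0.9 and 0.
- **26 weeks counted as well:** about 14-16%, or about 7-8% by the interval, at assumed outcome correlation 0.3-0.5 and time correlation 0.5-0.7. The 18.5% is only a ceiling for independent tests.
- **Both outcomes required:** joint power about 66-71% one-sided or 51-57% two-sided, for assumed correlation 0 to 0.5, instead of 0.80.

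The error rates apply when neither outcome has a true effect and one significant result is treated as success.

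**What to change.** Before any comparative results are seen, amend the protocol as follows.

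1. Name 8 weeks as the primary time point.
2. Make change in headache days at 8 weeks, the quantity on which the sample size is built, the first primary test.
3. Test medication use at 8 weeks only if headache days succeeds, at the same alpha.
4. Place the 26-week results later in the sequence or report them as supportive.

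The amendment should also say whether that alpha is the one-sided 0.05 of the sample size section or the level implied by the 95% intervals. At one-sided 0.05 the sequence keeps 35 (42 enrolled) per group. At two-sided 0.05, headache days would have about 70% power with 35.

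No patients are added at one-sided 0.05, which matters because the discussion calls recruitment the hardest part of the study. The cost is that medication use cannot be claimed unless headache days succeeds, so under the planned effects the chance of claiming both is the joint power of about 66-71%. The design already has ethics approval, so this is a substantive amendment and not just an edit.

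If the sponsor prefers to require both outcomes, no division of alpha is needed, but the power should be restated as about 66-71%. If either outcome is to suffice, dividing alpha needs 44 (52) per group.

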### Secondary outcome measures

The secondary outcome measures include:

* Headache pain intensity measured on a 10 point numerical rating scale (0 = no pain, 10 = most severe pain).

* The impact of headache on daily life will be scored by the patient using the Headache Disability Inventory (HDI) and the Headache Impact Test-6 (Hit-6). The HDI includes 25 questions on physical and emotional functioning with three possible response options: no = 0 points, sometimes = 2 points, yes = 4 points. A total score is computed by summating all scores, resulting in an individual HDI score ranging from 0 (no disability) to 100 (severe disability). A decrease in the total HDI of ≥ 16 points is considered to be a significant improvement. The test-retest reliability of the total score has been shown to be adequate (Pearson *r *0.76 for 1 week; *r *= 0.83 for 6 weeks) [25]

* The Headache Impact Test (HIT-6) consists of 6 items (pain intensity, social functioning, role functioning, vitality, cognitive functioning and psychological distress) each with 5 response options; never: 6 points, rarely: 8 points, sometimes: 10 points, very often: 11 points, always: 13 points, with a total score ranging from 36 to 78 points. Internal consistency (Cronbach alpha: 0.89) and test-retest reliability (ICC ranging from 0.78 to 0.90) have been demonstrated to be good.[26] The HIT-6 is able to differentiate between mild, moderate and severe headache. A between-group difference in HIT 6 change score of 2.3 points over time among patients with chronic daily headache reflects improvement in headache that may be considered to be clinically significant. [27]

* The active range of movement in flexion, extension, right and left rotation and right and left lateroflexion of the cervical spine with the patient in a seated position will be measured by the research assistant with the CROM-device. The intra- and intertester reliability have been shown to be good (ICC. > 0.80). [28]

* Algometry on the trapezius descendens and the suboccipital muscle will be performed with a Wagner FDK algometer with a 3.0 kg/cm pressure at four points at the left and right side: two points on the upper trapezius muscle and two points on the suboccipital muscle. Patients will rate the severity of pain on a 0–10 point NRS scale (0 = no pain, 10 most severe pain). Scores for each pressure point will be summated into a total score ranging between 0 and 80 points. Mechanical pressure algometry has been described by several authors as a valid measurement for pain pressure treshold for the trapezius muscle and has a good to excellent intertester- (ICC 0.70–0.91), intratester reliability (ICC 0.84–0.88) and a intra-individual coefficient of variation of 18.5% at 1 week test-retest. [29-31]

* Endurance of the neck flexor muscles will be scored as the number of seconds the patient can raise his head from the table when lying on his/her back. In a study of the neckflexor endurance test among subjects without neck pain Harris et al. reported good to excellent intratester reliability (ICC 0.82–0.91) and moderate intertester reliability (ICC 0.67–0.78).[32]

* A lateral digital picture with a digital HP R707.5 camera will be taken in a seated and standing position to measure the craniocervical angle. Recently van Niekerk et al. evaluated the criterion validity of photographic measurement compared with a digital radiographic device (LODOX) for assessing the craniocervical angle in sitting position among high school students (Pearson *r *0.89).[33] The reliability of photographic measurement of the craniocervical angle has been reported to be good in two studies(ICC >0.86). [33,34]

* Additional use of health care resources (including GP, psychologist, physiotherapist, acupuncture) will be reported by the patient at 26 week follow-up by completing a checklist. The patient will also be asked to report perceived improvement following treatment on a 7 point scale. (0 = much worse to 6 = much better).

